**Figure 1 fig1:**
[figure not shown]
Proposed design of the study and proposed outcome measures. EXP, experimental group; CON, control group; TAP, Test of Attentional Performance; SDMT, Symbol Digit Modalities Test; TMTA, Trail Making Test A; TMTB, Trail Making Test B; MoCA, Montreal Cognitive Assessment; 10-STS, 10 repetition sit-to-stand test; HGS, handgrip strength; TUG, Timedup and Go test; KDQoL-SF, Kidney Disease Quality of Life Short Form; BDNF, Brain-Derived Neurotrophic Factor; IL-6, Interleukin-6; hs-CRP, high-sensitivity C-reactive protein; Hb, hemoglobin; Hct, hematocrit.

#### Primary Study End Point

##### Cognitive Performance (Neuropsychological Assessment Battery)

Cognitive functions will be assessed with tests previously used in HD patients (Costa et al., 2014; San et al., 2017; Zimmermann and Fimm, 2017b; Jafari et al., 2020), including Montreal Cognitive Assessment (MoCA), Trail Making Test A and B (TMTA and TMTB), Symbol Digit Modalities Test (SDMT), and computerized Test of Attentional Performance (TAP).

TAP score is selected as the main outcome of this study. The rationale for the selection of the main outcome is: (i) absence of significant level of test-related learning effect (Zimmermann and Fimm, 2017b), (ii) sensitive to effects of physical exercise (Noguera et al., 2019), and (iii) attention is one of the most affected cognitive domains in dialysis patients (Dixit et al., 2013). From the TAP test battery, we will include subtests Alertness, Selective attention, Divided attention, and Sustained attention. Low to moderate training effects were reported for the TAP subtests (Zimmermann and Fimm, 2017a). The authors stated that performance remained stable in most of the TAP tasks at most of the testing occasions, suggesting that the performance in these tasks is robust and unaffected by learning effects or task repetition harassment.

MoCA (Nasreddine et al., 2005) is a global cognitive function assessment tool covering eight cognitive domains. The psychomotor speed and executive function will be measured by TMTA and TMTB (Corrigan and Hinkeldey, 1987). The SDMT will be used to assess the psychomotor speed, efficiency of information processing, ability to switch between mental sets of the information and to maintain and manipulate information in working memory (Smith, 1982; Benedict et al., 2017). It is a reliable and valid test for assessing information processing speed, efficiency and executive functioning domains (Benedict et al., 2017).

#### Secondary Study End Points

##### Physical Performance

We will test the patients with selected functional performance tests [10 repetition sit-to-stand test (10-STS), stork balance test, handgrip strength test (HGS)], exact methods already described in our previous study (Bogataj et al., 2020), with Timed Up and Go (TUG) test (Richardson, 1991; Ortega-Pérez de Villar et al., 2018), and spontaneous gait speed (Bučar Pajek et al., 2016).

##### Frailty Assessment

Frailty indicator will be assessed by the Edmonton Frail Scale (Rolfson et al., 2006; Garcia-Canton et al., 2019). The Edmonton Frail Scale assesses nine subscales: cognition, general health, functional independence, social support, medication use, nutrition, mood, continence, and functional performance in 11 items. The highest score is 17 points and correlates with the highest level of frailty (Rolfson et al., 2006). A score of 0–4 points represents no frailty, a score of 5–6 represents vulnerability, a score of 7–8 represents low frailty, a score of 9 to 10 represents moderate frailty, and a score above 11 represents severe frailty (Aygör et al., 2018).

##### Body Composition

Phase angle, fat, and lean body mass will be assessed with bioimpedance analysis (BCM Fresenius Medical Care).

##### Quality of Life

The participants’ quality of life will be assessed with validated Kidney Disease Quality of Life – Short Form questionnaire (Korevaar et al., 2002).

##### Blood Sampling and Potential Biomarkers (Biochemical Analysis)

The concentrations of the brain-derived neurotrophic factor (BDNF) will also be measured to explore the possible mechanisms underlying the effects of exercise on cognitive function. It was demonstrated that BDNF in the HD patients was significantly lower when compared to the age-matched control group (Zoladz et al., 2012). We decided to include BDNF biomarker in our analysis based on findings of Nofuji et al. (2012), reporting that the BDNF concentration was found to significantly change with physical exercise. Furthermore, a recent study showed that BDNF is associated with decreased physical performance and the prevalence of severe sarcopenia and frailty in HD patients (Miyazaki et al., 2021). Blood sampling will be performed by our staff (qualified HD nurses). Blood samples (∼7 ml) will be drawn *via* arteriovenous fistula before initiating HD procedure. Blood analysis will also include variables relevant to discuss the inflammation and HD-related laboratory parameters (such as CRP, urea, IL-6, and electrolytes).

##### Safety Parameters

The safety parameters assessed will be urea, creatinine, sodium, potassium, hemoglobin, hematocrit, self-reported falls, and musculoskeletal injuries.

### Statistical Methods Including Sample Size Calculation

The primary outcome of this study will be the cognitive function assessed with the subtest “Alertness” of the Test for Attentional Performance (TAP, Version 2.3; Psytest, 2012).

The sample size was calculated using G*Power software (version 3.1; Faul et al., 2009) on the basis of the results of the study by Briken et al. (2014). For the calculation, the scores of the subtest alertness from the TAP test battery which were obtained from the group that completed bicycle ergometry before (376.91 ± 151.67) and after (302.64 ± 83.09) the treatment were used. The alpha error probability was set to 0.05, the 1-beta error probability to 0.80, while the effect size was taken from the previously mentioned research (0.314). A sample size of 22 participants was calculated. Allowing for a 20% attrition rate, a total number of 27 participants is required, with 14 participants assigned to each group. Analyses will be conducted according to the intention-to-treat principle.

SPSS 24.0 (SPSS, Inc., Chicago, IL, United States) software will be used for all calculations. All data will be presented with mean ± standard deviation and 95% confidence intervals when appropriate. Normality will be confirmed by using the Shapiro–Wilk test, with additional Q–Q plot visual inspection. Independent-sample *t* test, *χ*^2^, or Mann–Whitney tests will be used to determine group differences in clinical and demographic variables, depending on the comparison and test assumptions. The main effects will be analyzed using a mixed general linear model (GLM), taking into account the groups (EXP and CON) and time (baseline and after 12 weeks) as factors. After determining the interaction effect, a secondary analysis will be used to determine the time effect in both groups. Additionally, the degree of effect will be determined for dependent variables by using partial eta-squared (*η*^2^). Partial eta squared readings of 0.02, 0.13, and 0.33 were rated differences as small, moderate, and high (Pierce et al., 2004). Furthermore, in the case of unmatched baseline means, the analysis of covariance (ANCOVA) with baseline measurements entered as a covariate will be applied. For non-parametric data, a Friedman ANOVA will be applied, followed by a Sign-test separately for each scale. Statistical significance will be set at values of *p* < 0.05.

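### The 80% power claimed for 22 participants rests on a one-group before/after change, and power for that same change as a between-arm difference is about 27%

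*Protocol article*

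**What the plan says.** All the planning figures are in the Protocol article, Statistical Methods Including Sample Size Calculation.

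- **Source of the effect:** Alertness scores "from the group that completed bicycle ergometry before (376.91 ± 151.67) and after (302.64 ± 83.09) the treatment". This is one arm of an earlier study, and no control-group change is given.
- **Error rates:** "The alpha error probability was set to 0.05, the 1-beta error probability to 0.80".
- **Effect and result:** "while the effect size was taken from the previously mentioned research (0.314). A sample size of 22 participants was calculated".
- **Allowance for dropout:** "Allowing for a 20% attrition rate, a total number of 27 participants is required, with 14 participants assigned to each group".
- **Primary analysis:** a mixed general linear model "taking into account the groups (EXP and CON) and time (baseline and after 12 weeks) as factors", read through the interaction.

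Study Interventions and Protocol sets 1:1 randomization to EXP or CON, and the Discussion states the hypothesis as improvement relative to control. The article does not name the G*Power test, the metric of 0.314 or the assumed correlation between baseline and 12 weeks.

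**The concern.** The planning effect and the primary test are different contrasts. A before/after change in one treated group includes practice, regression to the mean and anything else that would also move an untreated group. The interaction removes all of that by subtracting the control change. Even if the control change were zero, the same gain gives an interaction effect size only half as large as the one-group time effect, because only one of the two arms moves. An f computed for a one-group change and entered as an interaction f therefore doubles the assumed effect.

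If so, the primary test does not have the power stated for it. A non-significant result would be the likely outcome even if the whole cited gain were real, and it could be misread as evidence of no benefit.

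**Working it through.** **Inputs from the article:** means 376.91 and 302.64; SDs 151.67 and 83.09; alpha 0.05 (F test, equivalent to two-sided); target power 0.80; effect size 0.314; N = 22; two arms at 1:1; two time points. **Assumptions of this check:** correlation r = 0.5 (then varied), no change in CON, and scores in milliseconds (the article prints no unit).

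**1. Reproduce the plan's N.** For a 2 x 2 repeated-measures interaction, the noncentrality is λ = f² × N × m / (1 − r), with m = 2 and 1 and N − 2 degrees of freedom. With f = 0.314, N = 22 and r = 0.5: λ = 0.0986 × 22 × 2 / 0.5 = 8.68, and power = 0.800. N = 20 gives 0.757 and N = 24 gives 0.836.

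The smallest even N reaching 80% at other correlations is 42 (r = 0), 30 (0.3), 20 (0.6), 16 (0.7), 12 (0.8) and 8 (0.9). Of the values tried, only r = 0.5 returns 22. A one-group before/after test with dz = 2 × 0.314 = 0.628 also returns 22. A two-sample t test does not: it needs 322 in total for d = 0.314, or 82 for d = 0.628.

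**2. Find where 0.314 sits among the quoted data.** The change is 376.91 − 302.64 = 74.27. The root-mean-square SD is √[(151.67² + 83.09²)/2] = 122.29, and the simple mean SD is 117.38. For a one-group time effect, f = change / (2 × SD):

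- 74.27 / (2 × 122.29) = 0.304
- 74.27 / (2 × 117.38) = 0.316

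The stated 0.314 lies between these.

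**3. Put the same gain on the interaction scale.** If EXP changes by Δ and CON by zero, each of the four cells departs from additivity by Δ/4, so f = Δ / (4 × SD):

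- 74.27 / (4 × 122.29) = 0.152
- 74.27 / (4 × 117.38) = 0.158

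Conversely, f = 0.314 requires Δ = 4 × 0.314 × SD = 1.256 SD, which is 154 ms at SD 122.29.

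**4. Power for 74.27 ms at N = 22, r = 0.5.** With f = 0.152, λ = 2.03, about a quarter of 8.68, and power = 0.27. With f = 0.158, power = 0.29. Keeping the two quoted SDs unequal, the SD of change is √(151.67² + 83.09² − 151.67 × 83.09) = 131.55 and power is 0.24.

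**5. Vary the correlation** (two-sample t test on change, 11 per arm, Δ = 74.27):

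| r | Common SD 122.29 | Quoted SDs |
|---|---|---|
| 0.3 | 21% | 20% |
| 0.5 | 27% | 24% |
| 0.7 | 42% | 32% |
| 0.8 | 57% | 39% |
| 0.9 | 86% | 50% |

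**6. What 80% power would take at r = 0.5.** For 74.27 ms, the total number of completers is 82 with the mean SD, 88 with SD 122.29 and 102 with the quoted SDs. With 11 per arm, the detectable difference in change is 1.256 × 122.29 = 154 ms, or 1.256 × 131.55 = 165 ms.

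**The case against.** The origin of 0.314 is inferred. The article says only that the effect size came from the earlier study. Neither SD convention returns exactly 0.314, and the value also matches a partial eta-squared of 0.09, since √(0.09/0.91) = 0.314. If the source reported it for a group-by-time effect, the one-group charge would not apply as worded. This uncertainty stands, but the article does say that the one-group scores were the ones used. If 0.314 is instead a conversion from partial eta-squared, the matching noncentrality is f² × (N − 2) = 0.0986 × 20 = 1.97; power at 22 is again 0.27, and 84 would be needed.

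The 27% is conditional, and other inputs are kinder:

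- **Correlation.** A higher r raises power, as the table shows. But at r = 0.7 the plan's own calculation would have given 16, and at 0.9 it would have given 8.
- **A larger true difference.** The Introduction cites a pilot in which HD controls declined, and the Discussion expects most from the combined intervention. A 100 ms difference with common SD would give 45% (r = 0.5), 65% (0.7) or 82% (0.8). That is arguable, but it is not the planning effect stated. Pulling the other way, Primary Study End Point itself reports low to moderate training effects on TAP subtests, and any gain in CON lowers power.
- **No dropout.** With 14 per arm, power is 34% (common SD) or 30% (quoted SDs) at r = 0.5.
- **ANCOVA.** At r = 0.5 and 11 per arm it gives 35% with SD 122.29, or 63% if the post-treatment SD of 83.09 held in both arms (80% at r = 0.7). The article reserves ANCOVA for unmatched baseline means.

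None of these restores 80% for 74 ms at the correlation that reproduces 22.

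**Conclusion.** The concern holds. The sample size is built on a within-group change, while the primary test is a between-arm contrast, and the stated 80% does not follow from the quoted figures. For a true difference of 74.27 ms, power is about 24% to 29% depending on the SD used. The conditions are r = 0.5, no change in CON and 11 completers per arm. If the software run was instead a one-group before/after test, N is also 22 and the defect is the same. The precise percentage depends on the unstated correlation; the mismatch of contrasts does not. Because this is the power claim for the primary endpoint, it must be corrected.

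**What to change.** Keep the sample size and correct the statement. The paragraph should say:

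- 22 completers give 80% power only for a between-arm difference in change of about 1.26 SD (about 154 ms at SD 122 ms and r = 0.5).
- Power is about 27% for the 74 ms seen in the one-group source, under the same SD and correlation and no change in CON.
- The effect metric is f, with the assumed correlation given.
- The primary result will be read from the between-arm difference in milliseconds with its 95% CI, and non-significance will not be taken as absence of effect.

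The cost is wording in the protocol and SAP, and a less favourable power figure. It requires no extra patients.

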#### Study Interventions and Protocol

After the screening, recruitment, and baseline measurements, the patients will be randomized using sealed envelopes in 1:1 ratio into two groups:

– combined cognitive and exercise training (EXP) group and– control (CON) group

The EXP group will first exercise during dialysis (three times a week; 12 weeks) for ~30 min on a customized ergometer. They will start with a 3-min warm-up, and then, the resistance will be implied to each individual according to the rate of perceived exertion of 4th to 5th grade on a 10-grade Borg scale (Bogataj et al., 2020). After a break, they will be given tablets in order to play »cognitive stimulation games« on a CogniFit platform (~30–45 min). CogniFit “brain training” requires patients to repeatedly solve cognitively challenging tasks that target specific cognitive areas. These cognitive tasks are presented in the form of colorful, visually appealing “mini-games” to promote fun and enjoyment, thereby increasing motivation and engagement. The CogniFit platform offers a wide range of games (e.g., Jigsaw, Mandala, Sudoku, Puzzles, Word Quest, Piece Making, Tennis Bowling, and Line Changer, etc.). The difficulty level of the “brain exercises” automatically adjusts to the patient’s abilities as they practice and train. The cognitive areas targeted are: memory, reasoning, coordination, and attention with their subcategories. The training will be performed by a qualified kinesiologists (a professional coach experienced in prescribing and guiding the intradialytic exercise) and by a clinical psychologists with experience in cognitive testing of chronic patients. The CON group will receive standard HD care.

Graphically we present the study design in Figure 1. We plan to repeat the measurements 6 months after the end of the intervention to measure the longer-term retention effect of intervention.

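### The required total is given as 27, but 14 in each of two groups is 28, and 28 is the figure that the plan's own attrition allowance supports

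*Protocol article*

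**What the plan says.** The section on statistical methods and sample size in the protocol article gives the result of the power calculation in one short sentence: "A sample size of 22 participants was calculated". The next sentence allows for losses and sets the recruitment target: "Allowing for a 20% attrition rate, a total number of 27 participants is required, with 14 participants assigned to each group".

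The section on study interventions names two groups, EXP and CON, and fixes the allocation: "the patients will be randomized using sealed envelopes in 1:1 ratio into two groups". No third group is described, and the total is not restated elsewhere in the article.

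The error rates behind the 22 are also given: "The alpha error probability was set to 0.05, the 1-beta error probability to 0.80". The effect size is 0.314. Its type is not named, and the correlation between the two measurements is not stated.

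**The concern.** The sentence carries two recruitment targets. Read as a total, the target is 27. Read per group, it is 14 + 14 = 28. Both cannot be the planned number, and the text does not say that one was rounded to reach the other.

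The sentence also calls 27 the number required under 20% attrition. That can be checked against the 22 in the sentence before it, and 27 falls slightly short.

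What is at stake is small but practical. The target decides when enrolment closes, and the final report will be compared with it. A team working to the total would stop one participant earlier than a team working to the group size, with an expected number of completers just under the number the plan asks for. A team working to the group size would enrol enough, and readers would then find a total that differs from the published one.

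**Working it through.** **Inputs, all from the protocol article**
- Number needed before attrition: 22 in total (sample size section)
- Attrition: 20% (same section)
- Stated total: 27; stated group size: 14 (same section)
- Groups: 2, allocated 1:1 (study interventions section)
- Alpha 0.05, power 0.80, effect size 0.314 (sample size section)
- Primary model: group (EXP, CON) by time (baseline, 12 weeks) (sample size section)

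**Step 1. Can the 22 be reproduced?**
Yes, with two assumptions that the article does not state: 0.314 is Cohen's f, and the correlation between baseline and 12 weeks is 0.5. For the group-by-time interaction with m = 2 measurements, the noncentrality is

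λ = f² × N × m / (1 − ρ) = 0.314² × 22 × 2 / 0.5 = 0.098596 × 88 = 8.68,

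with 1 and 20 degrees of freedom. The power is 0.800 at N = 22 and 0.779 at N = 21, so 22 is the smallest total that reaches 0.80 under these assumptions.

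The 22 depends strongly on the assumed correlation:

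| Assumed ρ | Smallest N for power 0.80 |
|---|---|
| 0 | 42 |
| 0.3 | 30 |
| 0.5 | 22 |
| 0.7 | 15 |

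The remaining steps take the 22 as given and do not depend on ρ.

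**Step 2. Do the stated figures add up?**
2 × 14 = 28, against a stated total of 27. The difference is 1.

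**Step 3. What total keeps 22 after 20% loss?**
N = n / (1 − d) = 22 / (1 − 0.20) = 27.5, rounded up to 28. Per group: 11 / 0.80 = 13.75, rounded up to 14. The stated group size is therefore right and agrees with a total of 28.

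**Step 4. What does each total leave?**

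| Randomised | Expected after 20% loss | Largest loss that still leaves 22 |
|---|---|---|
| 27 | 27 × 0.80 = 21.6 | 5 of 27 = 18.5% |
| 28 | 28 × 0.80 = 22.4 | 6 of 28 = 21.4% |

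Only 28 covers the 20% allowance.

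**Step 5. Where could 27 have come from?**
Two routes lead to it: 22 × 1.20 = 26.4 rounded up, or 22 / 0.80 = 27.5 with the fraction dropped. The group size does not separate them, because 11 × 1.20 = 13.2 and 11 / 0.80 = 13.75 both round up to 14. The article does not show this step, so the origin of 27 cannot be determined.

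**The case against.** The strongest reply is that the same sentence already supplies an adequate number. A reader may take 27 as a minimum that was raised to 14 per group so that the arms would be equal. On that reading 28 will be randomised, 22.4 are expected to remain, and no shortfall arises. Nothing in the article contradicts this reading, and it answers most of the practical worry. It does not make 27 correct: the text calls it the required total, and as a minimum it is too low for 20% attrition.

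A second reply is that the effect is negligible. The expected shortfall at 27 is 22 − 21.6 = 0.4 of a participant. In whole people, five losses from 27 still leave 22. A sixth leaves 21, where power is 0.779 instead of 0.800 under an assumed correlation of 0.5. The 22 itself moves between 15 and 42 as that correlation goes from 0.7 to 0, and the 20% is a planning guess. All of this stands, and it keeps the point small.

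Three stronger readings are tempting, and the document does not support them:
- **That the randomisation envelopes cannot be prepared for 27.** A 1:1 ratio does not require an even final count. A set of 28 can be prepared and recruitment can end at 14 and 13. The article gives no envelope count.
- **That the authors multiplied by 1.20 instead of dividing by 0.80.** The figure fits that route, but it fits 27.5 rounded down equally well.
- **That the trial is underpowered by its own inputs.** The stated 14 per group meets the requirement of 22.

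**Conclusion.** The point holds as a small, certain correction. The stated total does not equal the sum of the stated groups, and of the two figures 28 is the one that follows from 22 participants and 20% attrition. The size is one participant: 21.6 expected completers at 27 against 22.4 at 28.

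The contradiction needs no assumption beyond there being two equal groups. The shortfall at 27 assumes only that the calculated 22 is the number meant to remain after attrition, which is how the article uses it. The discrepancy has a consequence only if enrolment is closed on the total rather than on the group size.

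This conclusion says nothing on whether 0.314, derived from the before-and-after change in one group of an earlier study, suits a comparison between two groups. That is a separate question.

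**What to change.** Change the total to 28 and show the attrition step, for example: *To retain 22 participants after 20% attrition, 28 will be randomised (22/0.80 = 27.5, rounded up), 14 per group.* If the total of 27 appears in other trial documents, such as the full protocol, correct it there as well.

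The cost is one number and a short clause. No recruitment is added beyond the 14 per group already planned, and the design and analysis are unchanged.

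### A normality check on 11 to 14 patients per arm decides whether Alertness gets a between-arm test at all, so the primary analysis is not fixed in advance

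*Protocol article*

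**What the plan says.** All of this stands in the protocol article under Statistical Methods Including Sample Size Calculation.

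- Primary outcome: "The primary outcome of this study will be the cognitive function assessed with the subtest “Alertness” of the Test for Attentional Performance".
- Main analysis: a mixed general linear model (GLM) with group (EXP, CON) and time (baseline, 12 weeks) as factors. The interaction is the between-arm comparison.
- Check: "Normality will be confirmed by using the Shapiro–Wilk test, with additional Q–Q plot visual inspection".
- Fallback: "For non-parametric data, a Friedman ANOVA will be applied", followed by a sign test for each scale.
- A further data-dependent switch: ANCOVA with baseline as covariate is used only if the baseline means turn out to be unmatched.
- Size: "A sample size of 22 participants was calculated", and "Allowing for a 20% attrition rate, a total number of 27 participants is required, with 14 participants assigned to each group". That is 11 evaluable and 14 enrolled per arm.
- Alertness figures, from the cited exercise study: "before (376.91 ± 151.67) and after (302.64 ± 83.09) the treatment".

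The section does not say whether raw values, change scores or residuals are checked, at what cutoff, or what happens if the test and the plot disagree. It does not exempt Alertness from the fallback.

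**The concern.** Read as written, the section tests the outcome data for normality and only then settles how they are analysed. At this size a non-significant Shapiro-Wilk test confirms little, and several such tests will sometimes reject perfectly normal data.

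The two branches also answer different questions. The GLM interaction asks whether EXP changed more than CON. Friedman and sign tests on repeated visits ask whether patients changed over time. If the switch occurs, the trial's only between-arm comparison of its primary outcome is replaced by within-patient tests. A change shared by both arms, such as practice, regression to the mean or a change in dialysis care, could then be reported as an effect.

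**Working it through.** **1. The plan's own sample size.** Inputs: "The alpha error probability was set to 0.05, the 1-beta error probability to 0.80"; "the effect size was taken from the previously mentioned research (0.314"), read as Cohen's f; two groups, m = 2 visits. The correlation ρ between visits is not stated; 0.5, the software default, is assumed. For the within-between interaction, λ = f²·N·m/(1−ρ) = 0.314² × 22 × 2/0.5 = 8.68 on F(1, 20), which gives power 0.800. So 22 is reproduced, and it was sized for the between-arm interaction, not for a Friedman test.

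**2. Shape assumption.** SD/mean is 151.67/376.91 = 0.40 before and 83.09/302.64 = 0.27 after. If lognormal, log-SD = √ln(1 + CV²) = 0.39 and 0.27. The lognormal shape is an assumption: the plan gives only means and SDs.

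**3. How often the switch occurs.** Simulation with the cited means and SDs, 11 or 14 per arm, visit correlation 0.5 or 0.7, Shapiro-Wilk at p < 0.05:

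| What is tested | Normal data | Lognormal data |
|---|---|---|
| Any of four arm-by-visit cells | 17–20% | about 49–67% |
| Model residuals, once | about 5% | about 15–40% |

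A separate run with the same log-SD at both visits gave lower residual-test figures under skew (8–17%).

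**4. Type I error of the gate by itself.** With no true arm difference and a between-arm rank test (Mann-Whitney on change) as a hypothetical fallback, the two-stage rule rejects in about 5% of trials. It costs at most about 2 power points against the stated GLM.

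**5. Type I error with the written fallback.** Let both arms change by the cited amount, 376.91 − 302.64 = 74.27, with no arm difference. With two visits the Friedman test depends only on how many of all N patients improve. For normal data:

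- SD of change = √(151.67² + 83.09² − 2r·151.67·83.09) = 131.55 (r = 0.5) or 110.75 (r = 0.7).
- P(a patient improves) = Φ(74.27/131.55) = 0.71, or Φ(74.27/110.75) = 0.75.
- Friedman rejects for 16 or more of 22, or 20 or more of 28, improving (or the mirror image). The binomial probability is 0.55 (N = 22, r = 0.5) to 0.745 (N = 28, r = 0.7).

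The two-stage rate is roughly P(switch) × P(Friedman rejects) + (1 − P(switch)) × 0.05:

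- any cell, normal data: 0.18 × 0.745 + 0.82 × 0.05 = 0.175;
- residuals, normal data: 0.05 × 0.55 + 0.95 × 0.05 = 0.075;
- residuals, lognormal data at the upper end: 0.40 × 0.72 + 0.60 × 0.05 = 0.32. Here 0.72 is the same binomial with P(improve) = Φ[(5.857 − 5.676)/0.277] = 0.74, from the lognormal parameters.

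This shortcut treats the switch as independent of the test result. Full simulation gives about **16–40%** on the any-cell reading and **7–31%** on the residual reading, the lower ends from normal data and the upper ends from lognormal data.

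With no shared change, the any-cell rule with Friedman keeps its level (4.4–5.3%) but loses power. Under the plan's effect size and correlation 0.5, it falls from 79–80% to 64–73% at 11 per arm, and from 87–88% to 66–81% at 14.

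**6. Is the gate needed?** Ungated, the between-arm contrast (GLM interaction or baseline-adjusted ANCOVA) has a type I error of about 4–6% under this skew.

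**The case against.** Four points can be made for the plan.

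- **The trigger is not spelled out.** No per-cell testing or cutoff is stated, Q-Q plots are added, and the normality assumption of a linear model concerns residuals. On that reading the switch is much rarer. This stands, and is why both readings are shown. But the missing rule leaves the choice open, and the plot adds judgement, not a rule.
- **The fallback may be meant for ordinal scales only**, such as the Edmonton Frail Scale. The wording allows this, but nothing limits it to them or exempts Alertness.
- **The cited SDs do not prove skew.** Zero lies 2.5 and 3.6 SDs below the two means, which is compatible with normality. This stands: the skewed figures depend on the lognormal assumption.
- **A pre-test does little harm by itself.** This also stands. A reader might infer that the method is picked largely by chance, or that the gate alone leaves the 5% level unprotected. The documents do not support either: with a between-arm fallback the level stays near 5%, and switching on skewed data is partly genuine detection of skew. A reader might also infer a power loss of 6 to 10 points. That compares the gate with an always-ANCOVA analysis, which is not the stated main analysis; much of it is lost baseline adjustment.

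**Conclusion.** The point holds in a limited form. The section makes the analysis of the primary outcome depend on a normality check whose object and cutoff are unstated, and one of the two branches contains no EXP–CON comparison. The damage comes from that combination: false-positive rates of about 16–40% or 7–31%, depending on the reading, if both arms change by the cited amount.

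These figures assume Shapiro-Wilk at p < 0.05 without the plot, normal or lognormal shape, visit correlation 0.5 to 0.7, and a shared change of 74.27. A smaller shared change gives less inflation, and none gives essentially none. The conclusion that the gate is unnecessary does not depend on the size of the shared change, because the between-arm contrast is unaffected by it. The point is worth correcting before analysis because the remedy costs almost nothing.

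**What to change.** In the statistical methods section, state that the primary analysis is one pre-specified EXP minus CON contrast on 12-week Alertness from the linear model, reported with its 95% CI whatever any normality test shows. Preferably include baseline Alertness as a covariate in all cases, which also removes the switch on unmatched baseline means. Use residual Q-Q plots descriptively only. Give a permutation test of the same contrast as the sensitivity analysis.

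The cost is a few sentences and a short permutation run. The downside is that the headline estimate stays a mean difference even if the data are skewed; the permutation test shows whether the inference depends on the normal approximation.
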